#### Health economics

The economic evaluation is based on the general principles of a cost-effectiveness analysis and cost-utility analysis. For the cost-effectiveness analysis we will calculate the incremental cost-effectiveness ratio (ICER) as cost per unit improvement on the HAQ. For the cost-utility analysis we will calculate the ICER as cost per Qaly gained. This ICER will be evaluated stochastically and uncertainty will be determined using the bootstrap method and/or Fieller method. A cost-effectiveness acceptability curve will be derived that is able to evaluate efficiency by using different thresholds (Willingness To Pay) for a QALY. The impact of uncertainty surrounding deterministic parameters (for example cost-prices) on the ICER will be explored using one-way sensitivity analyses on the range of extremes. The economic evaluation is done along-side the clinical trial and consequently adheres to the earlier presented design.

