#### Experimental intervention group

Patients (eight per group) allocated to the experimental intervention group attend six therapeutic group sessions and one group evaluation. During these six sessions patients aim to improve daily functioning by optimising their current lifestyle (i.e. physical activity and diet) and by enhancing self-efficacy to control the consequences of the disease in everyday life (i.e. activity pacing, pain management and daily functioning). To enhance patients' self-efficacy the 5As model of behaviour change counselling is used, which is an evidence-based approach appropriate for a broad range of different behaviours and health conditions. The 5As consists of: Assessing patient level of behaviour, beliefs and motivation; Advising the patient based upon personal health risks; Agreeing with the patient on a realistic set of goals; Assisting to anticipate barriers and develop a specific action plan; and Arranging follow-up support [36]. The following example might illustrate the use of the 5As model. A participant wears a pedometer to elicit his/her physical activity level (A1). Together with the health care provider, the patient discusses the outcome (A2) and set a goal to increase the level of physical activity (A3). Both the health care provider and the patient must believe the goal is adequate (A3) and realistic (A4). Consequently, patient and therapist closely monitor the personal goals (A5). In addition to the self-management programme, patients are also enrolled in an exercise programme aimed to 1. improve the quality of movement and 2. implement the learned exercises in the home situation.

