### Sample size

For the sample size calculation we used the statistical package G*power 3.0.10 [54]. We utilized the equation for sample size required per group using an unpaired t-test to compare differences between two independent means. To detect a minimal clinically important change of 0.26 points [39] in mean HAQ scores between both groups, assuming a SD of: 0.66 (SE*√N = 0.04*√271 = 0.66) [40] with 80% power and a two-sided 5% level, we will need 102 patients per arm (effect size is 0.26/0.66 = 0.39). The abovementioned sample size calculation is relevant for analyses with independent t-tests.

In our analyses, however, we will use the baseline HAQ as a covariate. By a straightforward generalisation of the method described in Borm et al [55], it can be shown that in this case the sample size must be multiplied by (1-(k-1)ρ)/k - ρ_B_^2 ^(see note below), where k is the number of follow-up assessments (3 in our case), where ρ_B _is the correlation between the outcome measured at baseline and at follow-up and where *p *is the correlation between the follow-up measurements. Although some publications report test-rest correlation for the HAQ of more than 0.8 (31), there is no direct information about the correlation that is to be expected in our trial. We expect ρ_B _to be smaller than *p *(even within the treatment groups), because the interventions will be 'between' the baseline and follow-up assessments. The interventions may not have the same effect on all patients and therefore decrease the correlation. When *p *is between 0.7 and 0.9 and ρ_B _= p-0.2, the sample size can be reduced by a (design) factor 0.44 to 0.55. For p between 0.8 and 0.9 and ρ_B _= *p*-0.1, the sample size can be reduced by a factor 0.38 to 0.44. A trial with 55 patients per treatment group will then have at least 80% power (when the design factor is 0.55). In the most optimistic scenario, when the design factor is 0.38, the study has slightly over 90% power.

Finally, as the patients will be treated in groups (cluster) of approximately eight, the patient numbers have to be increased by a factor 1+(8 -1)*ICC. For ICC = 0.05, this leads to 74 patients. In order to compensate for possible drop-outs (15%), we plan to enrol 85 patients per treatment group.

Note:

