#### Clinical efficacy

The primary variable, HAQ during the first year after treatment, will be analysed with a random effects model with the HAQ scores after 6, 26 and 52 weeks as dependent variable. The fixed factors will be assessment (6, 26 or 52 weeks), treatment group, sex and baseline value. In order to account for the group wise treatment and the repeated measurements, the random effects group and patient will be included.

HAQ immediately after treatment will be evaluated in a random effects model with fixed factors treatment group, sex and baseline value, and random factor group. All other continuous variables will be analysed in a similar way. Skewed variables will be transformed before analysis. For dichotomous outcomes, random effects general linear models with Bernoulli distribution and linear link function will be used, similar to the ones described for continuous outcomes.

Changes in effect size over time will be evaluated by adding the interaction of assessment and treatment group to the model.

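### The economic analysis names bootstrap and/or Fieller intervals without carrying over the therapy-group correlation; used at patient level, both would overstate certainty

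*Protocol article*

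**What the plan says.** Three parts of the Protocol article bear on this.

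- **Sample size.** The number per arm is inflated because, in the protocol's words, "as the patients will be treated in groups (cluster) of approximately eight, the patient numbers have to be increased by a factor 1+(8 -1)*ICC". The result is given as: "For ICC = 0.05, this leads to 74 patients".
- **Planned data analysis, Clinical efficacy.** The HAQ model contains random effects for group and patient. The reason given is: "In order to account for the group wise treatment and the repeated measurements". The remaining continuous outcomes are to be handled along the same lines.
- **Planned data analysis, Health economics.** Two ratios are planned, one per unit of HAQ improvement and one per QALY. For these, "uncertainty will be determined using the bootstrap method and/or Fieller method". In addition, "A cost-effectiveness acceptability curve will be derived that is able to evaluate efficiency by using different thresholds". The section closes with: "The economic evaluation is done along-side the clinical trial and consequently adheres to the earlier presented design". It names no resampling unit, variance estimator or group term.

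Grouping affects both arms. In the experimental arm, "Patients (eight per group) allocated to the experimental intervention group attend six therapeutic group sessions". Control patients have two sessions in groups of eight, followed by telephone contacts.

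**The concern.** The protocol twice treats membership of a therapy group as a source of correlation that matters. It then names a different inferential method for the economic evaluation and does not carry the grouping over. The usual bootstrap resamples individual patients, and the usual Fieller interval uses variances and a covariance computed across independent patients. If costs, QALYs or HAQ scores are positively correlated within a group, both understate the sampling variance of the between-arm differences.

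Cost-effectiveness is the stated secondary objective, and the Discussion expects the cost results to inform decisions by providers and care vendors. Intervals that are too narrow, and an acceptability curve that rises or falls too steeply with willingness to pay, would make the choice between programmes look more certain than the data allow.

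**Working it through.** **Inputs from the protocol.** Group size m = 8; ICC = 0.05 for HAQ; 55 patients per arm before the allowance for grouping; 74 after it; 85 enrolled. The ICC of costs and QALYs is not given. I assume a range of 0 to 0.10.

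**1. The protocol's own figure.** The design effect is DE = 1 + (m − 1) × ICC = 1 + 7 × 0.05 = 1.35. Then 55 × 1.35 = 74.25, against 74 stated. The step reproduces.

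**2. Effect of leaving the groups out.** An interval computed as if patients were independent has 1/√DE of the correct width. Its true coverage is 2Φ(1.96/√DE) − 1.

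| ICC | DE | Width relative to correct | Coverage of nominal 95% |
|---|---|---|---|
| 0 | 1.00 | 100% | 95.0% |
| 0.01 | 1.07 | 97% | 94.2% |
| 0.02 | 1.14 | 94% | 93.4% |
| 0.05 | 1.35 | 86% | 90.8% |
| 0.10 | 1.70 | 77% | 86.7% |

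**3. Weaker clustering in the control arm.** Suppose the ICC is 0.05 in the experimental arm and 0 in the control arm, with equal sizes and variances. The design effect of the difference is (1.35 + 1.00)/2 = 1.175, so √DE = 1.084. The interval has 92% of the correct width and covers 2Φ(1.96/1.084) − 1 ≈ 92.9%.

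**4. Simulation of a mean difference with few groups.** The protocol's numbers imply 74/8 ≈ 9 to 85/8 ≈ 11 groups per arm.

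- 9 groups of 8 per arm (1,500 trials, 400 draws each): the patient-level bootstrap covered 94% at ICC 0, 89% at 0.05 and 86% at 0.10. Resampling whole groups covered 92%, 89% and 92%. The Monte Carlo standard error is about 0.8 points (√(0.89 × 0.11/1500)).
- 11 groups of 7 per arm (3,000 trials, 600 draws each), ICC 0.05: patient-level bootstrap 90.3%, group bootstrap 91.3%, model with a random group effect 94.1%. The mean patient-level interval was 0.621 wide against 0.724 for the model, a ratio of 0.86, which agrees with step 2.

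The simulations therefore support the closed form. They also show that simple resampling by group does not restore 95% coverage with this few groups.

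**The case against.** The strongest case on the other side is that the article does not prescribe patient-level resampling. Both named methods can respect groups: the bootstrap by resampling them, Fieller by using cluster-adjusted variances and covariance. The resampling unit is a detail that a condensed article often leaves to an analysis plan, and none is shown here. The closing sentence of the Health economics section ties the evaluation to the trial design, and the clinical section extends its modelling approach to other continuous outcomes. Finally, the ICC of 0.05 was assumed for HAQ, and clustering may be weaker for costs and QALYs, particularly in the telephone arm.

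Much of this stands, and it limits the point in two ways.

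- A reader might infer that the protocol has chosen to disregard the groups. The text does not say so, and the shortfall in coverage is conditional on patient-level use and a positive ICC.
- A reader might also infer that the HAQ difference must carry a smaller standard error in the economic analysis than in the clinical one. That does not follow, because the clinical model also adjusts for baseline. With the protocol's scenario of follow-up correlation 0.7 and baseline correlation 0.5, the adjusted and clustered variance factor is 0.55 × 1.35 = 0.74. The unadjusted, unclustered factor is (1 + 2 × 0.7)/3 = 0.80, which is larger.

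The two general sentences do not settle the matter. Following the trial design most naturally refers to arms, follow-up and measurements, and supplies no cluster adjustment. The sentence on other continuous outcomes stands under Clinical efficacy, whereas the ratios have their own named method in a separate section.

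**Conclusion.** The point holds in conditional form. The protocol fixes a method for economic uncertainty that, in its usual form, assumes independent patients, and it does not extend to that method the group correlation it accounts for elsewhere.

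If the methods are applied at patient level with groups of eight, the loss ranges from none at ICC 0 to about 8 points of coverage at 0.10. At the protocol's HAQ value of 0.05 the interval would have about 86% of the correct width and cover about 91%. That value applies most directly to the HAQ side of the cost-per-HAQ ratio; for costs and QALYs it is an assumption. The calculations rest on equal ICCs in both arms (except in step 3) and concern a mean difference, not the ratio itself. The direction carries over to the ratios and the acceptability curve, but the exact size may differ.

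**What to change.** State in the Health economics section that the uncertainty analysis accounts for therapy group. Either of these would serve:

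- **Net benefit.** For each willingness-to-pay value, compute each patient's net benefit (threshold × QALY − cost). Analyse it with the same random group effect and baseline adjustment as the clinical outcomes, and derive the acceptability curve from that model.
- **Fieller.** Use cluster-adjusted variances and covariance for both ratios. This suits cost per HAQ unit in particular, since the protocol defines thresholds only for a QALY; a net-benefit analysis there would need an assumed range of values per HAQ point.

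Any bootstrap should resample cost and effect jointly, with the therapy group as the unit. The text should acknowledge that simple group resampling still under-covers (about 89% to 92%) with roughly 9 to 11 groups per arm, so it should not be the only basis for the intervals.

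The cost is small: a sentence or two of text, slightly more programming and somewhat wider intervals (about 16% wider at ICC 0.05, since √1.35 = 1.16). No new data are needed, because the clinical model already requires group membership.

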## Discussion

To date, research on NPT options for OA has mainly focused upon patients with hip and knee OA. In 2008, NICE disseminated multiple recommendations for future OA research based on the research hiatuses they identified. One of their research questions was: "What are the benefits of individual and combination OA therapies in people with multiple joint region pain?". This study will contribute to the body of evidence on NPT in GOA patients.

A possible limitation in our study is the limited contrast in the content of the experimental and control intervention. Both interventions were developed from a clinical and pragmatic perspective. Since both interventions should be directly implementable in clinical practice after study completion, we created two treatment protocols according to the recommendations outlined in OA guidelines and current best-practice. The content of both interventions is very similar but several critical differences are apparent such as the mode of delivery, the number of involved health care providers and the number of group-sessions. Specific insights in the effectiveness and costs of these differences will aid health care providers and care vendors in their decision making for the management of patients with GOA.

To our knowledge we are the first to define GOA from a clinical rather than a radiographic perspective, as no consistent clinical useful definition of GOA is available. In 1952, Kellgren and Moore defined GOA as involvement of multiple joints combined with Heberden's nodule [31]. Since then, multiple definitions of GAO have been used, for the greater part based on radiological changes. Most definitions state that GOA involves at least three joints [31], although this again is questioned [27]. The group of joints most often incorporated in definitions are the hands, neck, lower back, knees and hips [7,56,57], whereas other definitions postulate that the involvement of atypical joints [25,26] or hallux valgus [25,58] is essential for GOA. To date, two specific phenotypes of GOA have been established [28], however, these phenotypes are far from useful in daily practice as these phenotypes only represent a very small proportion of patients with OA-like complaints in multiple joints. Considering the low feasibility and desirability of obtaining radiographs of a large number of joint in clinical practice, we believe that clinical signs and symptoms should also be taken into account in the definition of GOA. Especially, since pain at multiple joint sites is associated with lower levels of functioning [21,23,59-61], more pain [21,23,59,60] and higher levels of distress [21,59,62], and complaints rather than radiographic OA are the main motivation for patients to engage in therapy. So, for the purpose of this project we formulated a pragmatic definition of GOA (as described earlier) based upon literature findings and on the basis of consensus of several clinicians and health professionals with experience with patients with GOA.

There is a need for outcome measures to evaluate self-management interventions [63]. Self-management is defined as the individual's ability to manage the symptoms, treatment, physical and psychosocial consequences and lifestyle changes inherent in living with a chronic condition [64]. Characteristically, one or more of these areas are addressed by self-management interventions [63]. In our study we target physical functioning, pain, fatigue, physical activity, and acceptance. However, no comprehensive outcome measure is available to measure all these different aspects. Mulligan *et al *(2005) state that when designing a self-management intervention, it is important to be clear about what the intervention is designed to achieve, in what areas it is likely to have an effect, and to choose outcome measures accordingly [63]. Therefore, we decided to include a responder analysis - derived from the OMERACT-OARSI responder criteria [46] - as one of the secondary measures in our analysis that specifically evaluates those areas we aim to address. In a future publication we intend to evaluate and discuss this method of assessing self-management interventions.

In conclusion, this study will provide additional insights in the effectiveness of non-pharmacological interventions for GOA. The publication of our study protocol enables future readers to compare what was originally intended with what was actually done, thus preventing both "data dredging" and post-hoc revisions of study aims.
